## Abstract

**Background:**

Employees in health care service are at high risk for developing mental health complaints. The effects of mental health complaints on work can have serious consequences for the quality of care provided by these workers. To help health service workers remain healthy and productive, preventive actions are necessary. A Workers' Health Surveillance (WHS) mental module may be an effective strategy to monitor and promote good (mental) health and work performance. The objective of this paper is to describe the design of a three arm cluster randomized controlled trial on the effectiveness of a WHS mental module for nurses and allied health professionals. Two strategies for this WHS mental module will be compared along with data from a control group. Additionally, the cost effectiveness of the approaches will be evaluated from a societal perspective.

**Methods:**

The study is designed as a cluster randomized controlled trial consisting of three arms (two intervention groups, 1 control group) with randomization at ward level. The study population consists of 86 departments in one Dutch academic medical center with a total of 1731 nurses and allied health professionals. At baseline, after three months and after six months of follow-up, outcomes will be assessed by online questionnaires. In both intervention arms, participants will complete a screening to detect problems in mental health and work functioning and receive feedback on their screening results. In cases of impairments in mental health or work functioning in the first intervention arm, a consultation with an occupational physician will be offered. The second intervention arm offers a choice of self-help e-mental health interventions, which will be tailored based on each individual's mental health state and work functioning. The primary outcomes will be help-seeking behavior and work functioning. Secondary outcomes will be mental health and wellbeing. Furthermore, cost-effectiveness in both intervention arms will be assessed, and a process evaluation will be performed.

**Discussion:**

When it is proven effective compared to a control group, a WHS mental module for nurses and allied health professionals could be implemented and used on a regular basis by occupational health services in hospitals to improve employees' mental health and work functioning.

**Trial Registration:**

NTR2786

## Background

Common mental disorders (CMDs) can have negative effects on work as they can impair work functioning and increase sickness absence [1-5]. In some occupations, the impairments in work functioning can have serious consequences, such as injuries to workers. One occupation in which this vulnerability is highly present is nursing. Nurses, the largest occupational group in healthcare, are at higher risk of developing mental health problems compared to workers outside of the health care sector and compared to other (health) service workers [6]. The relative risk for depression is high for nurses, RR = 3.5, 95% CI (1.3, 9.6), compared to other human service workers and other healthcare workers [6]. This high risk might partly be explained by the very nature of the work, with work environment characteristics that are known to promote the occurrence of mental health complaints, such as high job demands, low job control and low social support [7,8]. Furthermore, in the health care sector, impairments in work functioning can have serious effects not only for the nurses but also for patients and their safety as a recent literature review showed [8,9].

In the Netherlands, the occupational health care that is provided for employees with mental health problems can be considered effective. Care according to the guidelines for occupational physicians' (OP) treatment of workers with mental health problems has been proven to improve mental health and to enhance return to work for sick-listed employees [10,11]. However, the health service for OPs is often not used by workers until they are sick-listed. Late or no help-seeking for mental health complaints is a well-known problem inside and outside of the occupational health service [12,13]. Preventive actions are needed to provide timely help before work functioning is reduced to the extent that workers cause serious incidents or must call in sick. Early identification of health complaints and risks in work functioning to provide timely help is a first step in the prevention of more serious consequences for the health and safety of the nurses and their patients. Furthermore, preventive actions can improve the wellbeing of employees in the health care sector. Wellbeing can have positive effects on the engagement and productivity of employees. With the age of the caring workforce increasing, the importance of sustainable labor participation by senior employees is increasing. Therefore, it is of utmost importance to keep the caring work force engaged and mentally fit so they can continue to meet the high mental demands of modern-day work.

A Workers' Health Surveillance (WHS) mental module may be a successful preventive strategy for CMDs and impairments in work functioning in the health care sector. Within the occupational health care setting, WHS is a well-developed strategy for preventive actions [14,15]. WHS aims to detect negative health effects of work in an early stage to enable timely interventions [15]. Although the use and application of WHS is rising for various occupations and health effects, little is known about WHS targeting mental health effects. In a recent literature review by Plat et al. [16] on WHS in military and emergency service personnel, three studies included psychological health aspects, one in police personnel [17], one in rescue and recovery workers [18] and one in soldiers [19]. WHS for mental health effects in nurses has not yet been scientifically evaluated. Therefore, the aim of this study is to test the effectiveness of a job-specific WHS mental module for nurses and allied health professionals.

Although the International Labour Organization has formulated recommendations for the use of WHS, the design differs between countries. In the Netherlands, a policy guideline on how to conduct WHS exists [20]. This guideline does not prescribe any specific interventions, but includes principles and leading criteria such as the statement that screening for health problems should only be conducted if effective interventions for that health problem are available. Furthermore, one of the core aims of the guideline is the monitoring and improvement of both the health and functioning of workers. Therefore, our job-specific WHS mental module includes screening for early signals of mental health complaints and for impairments in work functioning. For the detection of impaired mental health, several validated instruments exist that are suited for the working population. However, until recently, no instrument for detecting impaired work functioning in healthcare workers related to mental health problems was available. Such an instrument has now been developed to be used in the hospital environment, the Nurses Work Functioning Questionnaire (NWFQ) ([name], [name], [name], [name], unpublished). The NWFQ was designed based on literature studies and focus group investigations with the workers' supervisors, human resource managers and occupational health professionals. The NWFQ has a high content validity, and its seven subscales show good or acceptable internal consistency.

For the interventions that follow the screening, two different strategies were developed. The first strategy is a consultation offered by the OP following a protocol for care for workers with mental health complaints, as developed for this study. The second strategy is a choice of self-help e-mental health interventions that is offered to all workers - those with and without complaints. The choice is tailored to the individual screening results.

The objective of the Mental Vitality @ Work study is to study the effectiveness of two strategies for the WHS mental module in one cluster randomized controlled trial design with three arms. Substudy 1 aims to test the effectiveness of screening for problems in mental health and work functioning plus advice on appropriate interventions by an OP compared to a control group. It will study the effects on adequate help-seeking behavior, work functioning and mental health. We hypothesize that employees who receive the WHS mental module with screening plus an invitation for OP-care will show more adequate help-seeking behavior than employees in the control group. Furthermore, we hypothesize that work functioning and mental health problems will improve in employees who receive the WHS mental module with screening plus invitation for OP-care compared to employees in the control group.

Substudy 2 aims to compare the OP-care strategy with a second strategy, including the same screening of problems in mental health and work functioning as in the OP-care strategy plus a stepped care e-mental health approach. Substudy 2 will compare the effects of both strategies on work functioning and mental health. We hypothesize that both WHS mental module strategies are equivalent in their effectiveness on work functioning, mental health and wellbeing compared to the control group. An economic evaluation of the WHS mental module will be conducted alongside the randomized controlled trial. Cost-effectiveness of the WHS mental module will be assessed from a societal perspective. The employer's perspective will be considered in a cost-benefit analysis. Regarding cost effectiveness, we hypothesize that the WHS mental module with E-mental health interventions is more cost effective than the WHS mental module with OP-care.

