### Study design

A cluster randomized controlled trial with three parallel arms will be performed in order to evaluate the effectiveness of two strategies for a WHS mental module for nurses and allied health professionals: the OP-care strategy and the E-mental health strategy. The study combines two separately funded substudies. Substudy 1 will compare the control arm with the OP-care arm - a screening on mental health complaints and impaired work functioning followed by a consultation with an OP and appropriate interventions if necessary. Substudy 1 will test the effect on help-seeking behavior, work functioning and mental health of employees with problems in mental health and/or work functioning.

Substudy 2 will compare the E-mental health arm - a screening on mental health complaints and impaired work functioning followed by a tailored choice of self-help e-mental health interventions - with the control arm and with the OP-care arm. Additionally, a subgroup analysis of the healthy participants comparing the E-mental health arm with the OP-care arm will be conducted. Substudy 2 will test the effect of the interventions on work functioning and mental health.

Participants will be followed for six months. Two follow-up measures will be conducted, one at three months and one at six months. The Medical Ethics Committee of the Academic Medical Center in Amsterdam (AMC) gave approval for the study. Figure 1 presents an overview of the study design. Below, differences between Substudy 1 and Substudy 2 are described. Otherwise, the information is equal for both parts.

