#### Primary outcomes measured at baseline, three month follow-up and six month follow-up

##### Substudy 1

The primary study parameter of the comparison between the OP-care arm and the control arm is help-seeking behavior. It regards formal help sources that the subject has used during the past three months. In the operationalization of formal help sources, 11 help sources are presented (i.e., psychologist, psychiatrist, general practitioner, OP, physiotherapist, supervisor, coach, in-company social worker, social worker, religious counselor, alternative therapeutic treatments). The list of help sources is developed in analogy with earlier studies on help-seeking behavior [61-64].

The outcome measure help-seeking behavior is dichotomized into 'did seek formal help' for participants who had made use of any of the 11 caregivers and 'did not seek formal help' if none of the 11 caregivers were visited.

##### Substudy 2

The primary outcome measure of the comparison of the E-mental health arm with the OP-care and the control arm is work functioning, operationalized as job-specific impairments in work functioning. It will be measured using a total score of the Nurses Work Functioning Questionnaire (NWFQ).

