#### Sample Size

##### Substudy 1

In a study by Isaaksson Ro [78] on help-seeking behavior in nurses with burnout, the formal help-seeking increased from 17% to 34%. Differences between the percentages of participants having sought formal help between the two study arms will be examined using a Chi-square test. For an increase of 17% with alpha = 0.05 (2-tailed) and a power of (1-beta) = 0.80, power calculation using the Nquery Advisor software results in 114 participants with mental health complaints for each of the two arms. Based on data from a prior study in this population ([name], [name], [name], [name], unpublished), we assume that 50% of the population will have impairments in either mental health, work functioning or both. Thus, for a comparison of workers screened positive in the control arm and the OP-care arm, 228 participants in each arm are necessary. Randomization will take place at the ward level; however, we do not expect any correlation between wards in the help-seeking behavior of their employees. Therefore, no inflation factor is used in the power calculation for Substudy 1 with the outcome measure help-seeking behavior. With an expected loss-to-follow-up of 10%, we must start the trial with N = 228/0.90 = 254 per condition at baseline.

##### Substudy 2

The trial is powered to detect a clinically significant effect, defined as at least 0.33 standard units when the (primary) outcome is transformed into a standardized effect size, also known as Cohen's d or the standardized mean difference. Lipsey and Wilson [79] conducted a second-order meta-analysis of psychological, educational and behavioral interventions and found that for these interventions, d = 0.33 to be corresponding with the lower bound of a medium effect size. We will conduct tests at alpha = 0.05 (2-tailed) and a power of (1-beta) = 0.80. Using Stata, it is shown that n = 145 per condition is required. For the primary outcome measure of this substudy, work functioning, no information on probable difference on ward-level exists. But as a precaution, we compensate for possible cluster effects introduced into the data because of randomization on ward-level. For cluster correction, we must multiply by a factor 1.3, which returns 145*1.3 = 189 per condition. Assuming a loss-to-follow-up of 10%, we must start the trial with N = 189/0.90 = 210 per condition at baseline.

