##### Effect evaluation

To study the effect on dichotomous outcome measures Chi-square tests will be used; thus, to test differences in proportions of subjects who score positive on the outcome measure between the study arms for each time of measurement. Change of proportion of employees in outcomes at follow-up (T1 and T2) will be analyzed using Generalized Estimated Equations (GEE), with wards and participants as cluster variables (where appropriate) and study-arm, time and their interaction (study-arm × time) as co-variates under the assumptions of an exchangeable working correlation matrix. Effects of demographic characteristics and prognostic factors on dichotomous outcomes measures will also be analyzed using Generalized Estimated Equations (GEE).

Effects of continuous outcome measures will be analyzed using multiple regression analysis. A multilevel analysis of variance will be conducted (GLM mixed models, repeated measurements), with ward as the primary hierarchical level and participants as the secondary hierarchical level (where appropriate). Effects of demographic characteristics and prognostic factors on continuous outcome measures will also be analyzed using multiple regression analysis.

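### Substudy 2 hypothesises that the two strategies are equivalent, but is sized and analysed only for a difference, with no margin or confidence-interval rule

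*Protocol article*

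**What the plan says.** The objective at the end of the Background gives the Substudy 2 hypothesis as: "We hypothesize that both WHS mental module strategies are equivalent in their effectiveness on work functioning". The sentence goes on to name mental health and wellbeing as well, and ends with a reference to the control group. Study design says that Substudy 2 compares the E-mental health arm "with the control arm and with the OP-care arm". The primary outcomes section makes both comparisons primary: "The primary outcome measure of the comparison of the E-mental health arm with the OP-care and the control arm is work functioning", measured by the NWFQ total score.

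The Sample Size section then takes a difference approach for Substudy 2: "The trial is powered to detect a clinically significant effect, defined as at least 0.33 standard units". It continues: "We will conduct tests at alpha = 0.05 (2-tailed) and a power of (1-beta) = 0.80", and "Using Stata, it is shown that n = 145 per condition is required". That number is multiplied by 1.3 for clustering (189) and divided by 0.90 for loss to follow-up (210 per condition).

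Under Effect evaluation, the plan is: "Effects of continuous outcome measures will be analyzed using multiple regression analysis", followed by a multilevel repeated-measures model. The article gives no equivalence margin, no rule based on a confidence interval and no sample size for equivalence. It does not say how a non-significant difference between the two strategies would be interpreted.

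**The concern.** A hypothesis of equivalence and a test for a difference ask opposite questions. In a difference test the null hypothesis is that the strategies are the same, so failing to reject it may only reflect limited precision. To support equivalence, the data must exclude differences larger than a stated margin, and the article states none.

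The sample size and the direction of testing are fixed in this document, and both are for a difference. The between-strategy part of a primary-outcome hypothesis therefore has no test that could confirm it. At stake is whether the trial may say at the end that the two strategies do equally well for work functioning.

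**Working it through.** **Inputs from the Sample Size section:** difference to detect 0.33 SD; two-tailed alpha 0.05; power 0.80; 145 per condition; cluster factor 1.3; loss to follow-up 10%; baseline minimum 210 for Substudy 2 and 254 per condition for Substudy 1. **Assumptions:** equivalence margins of 0.33, 0.25 and 0.20 SD, because the article gives none; a true difference of zero for equivalence power; normal approximation.

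**1. The plan's own figure.** n = 2 × (1.96 + 0.842)² / 0.33² = 144.2, rounded up to 145. Then 145 × 1.3 = 188.5, rounded up to 189, and 189 / 0.90 = 210. The stated figures reproduce exactly from the formula for detecting a difference. Power at 145 per arm is 80.2%.

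**2. What a non-significant result would mean.** With 145 effective per arm, SE = √(2/145) = 0.117 SD. The 95% CI half-width is 1.96 × 0.117 = 0.23 SD, and the 90% CI half-width is 1.645 × 0.117 = 0.19 SD. The probability of a non-significant difference is one minus power:

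| True difference (SD) | P(non-significant) |
|---|---|
| 0.20 | 60% |
| 0.25 | 43% |
| 0.33 | 20% |

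**3. Effective arm sizes for E-mental health against OP-care.** E-mental health: 210 × 0.90 = 189, and 189 / 1.3 = 145. OP-care, at the 254 required by Substudy 1: 228 after loss to follow-up, and 228 / 1.3 = 175. (The summary of the arms calls both the second 254 and the 210 intervention arm 2. The 254 is read here as OP-care, since it comes from Substudy 1.)

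**4. Power for equivalence by two one-sided tests (TOST)** at one-sided 0.05, that is, the 90% CI lying inside the margin: power = 2Φ(margin/SE − 1.645) − 1. SE is 0.117 for 145 against 145. For 145 against 175 it is √(1/145.4 + 1/175.4) = 0.112.

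| Margin (SD) | 145 vs 145 | 145 vs 175 |
|---|---|---|
| 0.33 | 76% | 80% |
| 0.25 | 37% | 44% |
| 0.20 | 5% | 11% |

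For example, at 0.33 SD with equal arms: 0.33/0.1174 − 1.645 = 1.165, Φ = 0.878, and power = 0.756.

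**The case against.** The strongest defence lies in the end of the hypothesis sentence, which refers to the control group. It can be read as saying that both strategies improve on control to a similar degree, and the 0.33 SD sizing does suit each comparison with control. The ambiguity is real. But to a similar degree is still a statement about the two strategies relative to each other, and two separate wins over control do not establish it. On either reading, the between-strategy part has no margin and no test.

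It is also fair to say that a confidence-interval rule may stand in an analysis plan not shown here. That would help, but the sample size and the test direction given in this article would still be for a difference. The repeated-measures model could also give better precision than the two-sample figures above. The article gives no correlation, so the gain cannot be quantified, and it would not supply a margin.

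A reader might infer several stronger claims that the article does not support:

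- **That non-significance will be read as equivalence.** The article nowhere says so. The point is only that it offers no other route to its hypothesis.
- **That a false claim of equivalence is highly probable.** At the trial's own threshold the figure is 20%. The 60% and 43% apply to differences of 0.20 and 0.25 SD, which lie inside a 0.33 SD margin.
- **That the trial is too small for equivalence at 0.33 SD.** With equal arms, 158 effective per arm would be needed, or 229 at baseline against 210. This ignores the larger OP-care arm, which brings power to about 80%.
- **That the cost-effectiveness analysis depends on equivalence.** The planned ratio, planes and acceptability curves use the estimated effect difference and its uncertainty, and need no equivalence verdict.
- **That healthy participants dilute a difference.** E-mental health is offered to them too, whereas an OP invitation is not, so their effect on the contrast could go either way.

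**Conclusion.** The mismatch stands: an equivalence hypothesis on the primary outcome is paired with a sample size and analyses for a difference. It does not depend on which margin is chosen. Only the consequence for power does. At 0.33 SD the planned arms give about 76–80% power and no extra participants are needed. At 0.25 SD power is 37–44%, and at 0.20 SD it is 5–11%. These figures rest on assumed margins, a true difference of exactly zero, a 90% CI rule, and the plan's own cluster factor and loss to follow-up. A true difference other than zero would lower them.

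**What to change.** State two questions for Substudy 2 separately.

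1. Superiority of E-mental health over control, for which the present 0.33 SD sizing is suitable.
2. E-mental health against OP-care, in one of two forms:
   - Fix a justified margin, no wider than 0.33 SD, before data are seen. Declare equivalence only if the 90% CI for the difference lies wholly inside it (TOST), and give the power at that margin in the Sample Size section.
   - If no margin can be justified, replace the word equivalent by an aim to estimate the difference with its CI, and state that a non-significant result will not be called equivalence.

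The hypothesis also names mental health and wellbeing. Unless margins are set for those outcomes too, they should take the estimation wording.

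The cost is a rewording of the hypothesis and analysis and one added power statement. Recruitment, data collection and the models are unchanged. The downside is that a margin tighter than 0.33 SD would have to be reported as underpowered.
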